**Figure 1 figure1:**
[figure not shown]
Mid rectal T3 tumor < 5 mm EMD and predicted CRM > 1mm. No suspicious lymph nodes and no EMVI. T: primary tumor; EMD: extramural depth of invasion; CRM: circumferential resection margin; and EMVI: extramural venous invasion.

### Radiologic Assessment

Each MRI will be reported according to the standard protocol for the study [14]. At minimum, the MRI protocol must include high resolution, axial oblique T2 weighted sequences. The MRI report must include: (1) distance to the mesorectal fascia (predicted CRM), (2) T-category (includes, primary tumor, discontinuous tumor nodes, suspicious lymph nodes, and extramural venous invasion; definite T1 and T1/early T2 tumors will be excluded from study protocol) including extramural depth of invasion into the mesorectum (EMD) for all tumors T3 or greater, (3) absence or presence of suspicious lymph nodes, and (4) absence or presence of extramural venous invasion (EMVI). Although presence of suspicious lymph nodes is not a MRI criterion for “good prognosis” tumors, this information will be recorded so that we will be able to assess the accuracy of lymph node assessment on MRI compared to the final pathology since all patients are undergoing primary surgery. If there is any uncertainty regarding these MRI criteria, the reporting radiologist will be instructed to review the MRI with the Site Lead Radiologist to achieve consensus. If consensus is not achieved and/or uncertainty still exists after review by the Site Lead, the reporting radiologist will be asked to contact the Lead Radiologists (LM, MF) for the study for central review. The central study office (SS, EK) will review the MRI reports to ensure that all of these MRI criteria are reported. In the case of missing data, the Radiology Site Lead will be contacted to obtain this data. Participating centers and radiologists will be encouraged to use a synoptic MRI template for the study; however, this is not mandatory for participation in the study [15]. Prior to the start of the study, a Radiology Webinar will be organized to review MRI protocol, definitions, and interpretation of MRI criteria, and educational materials will be provided. In addition, Radiology training sets will be developed and will be required to be successfully completed by participating radiologists.

### Surgical Assessment

The surgical procedure will be left to the discretion of the surgeon and will involve a partial mesorectal excision for upper rectal cancers (above the anterior peritoneal reflection) and total mesorectal excision (TME) for mid and low rectal cancers (below the anterior peritoneal reflection) [16]. To be eligible for the study, surgeons must have completed colorectal or surgical oncology fellowship training in Canada or the United States. Surgeons will also be encouraged to use a synoptic Operative Report template that has been pilot tested and is currently being used in British Columbia; however, this is not mandatory for participation in this study [17]. The central study office (SS, EK) will review the surgical reports to ensure that all of the surgical information required is reported. In the event that there is missing data, the treating surgeon and Site Lead will be contacted.

Surgery should occur as soon as possible from the time of decision for surgery. Prior to the start of the study, participating surgeons will be required to attend the Pathology Webinar in which the protocol for gross evaluation of the TME specimen will be reviewed and discussed. Participating surgeons will be provided with educational materials and will be encouraged to present cases with positive CRM or incomplete TME at MCC for feedback and audit from the site group.

### Pathologic Assessment

Each surgical specimen will be processed and reported according to the standard protocol by Quirke et al and must include both macroscopic (quality of the TME) and microscopic assessment (including T-category; EMD; EMVI; and N-category, regional lymph nodes) [18]. Photographs of the gross specimen and serial section are required. If there is any uncertainty about any of these criteria, the reporting pathologist will be instructed to have this reviewed by the Site Lead to achieve consensus. However, if consensus is not achieved or uncertainty still exists after review by the Site Lead, the Site Lead will be asked to contact the Lead Pathologists (RK, DD) for central review. The central study office (SS, EK) will review the pathology reports to ensure that all of the required criteria have been reported. In the case of missing data, the Pathology Site Lead will be contacted to obtain the missing data. Prior to the start of the study, a Pathology Webinar to review the Quirke method will be organized. At the webinar, there will be a review of the Quirke protocol and definitions and interpretation of the reported criteria. Educational materials will be provided and a Pathology training set will be developed and will be required to be successfully completed by participating pathologists. Participating pathologists will be encouraged to use the College of American Pathologists checklist, however, this is not mandatory for participation in the study [19].

### Recommended Follow-Up

Figure 2 shows the recommended follow-up for the study. For patients with a negative CRM and no lymph node involvement, no further treatment will be recommended and these patients will be placed in a surveillance program as per the institutional protocol. However, chemotherapy may be considered in these patients if there are other high risk features such as EMVI present. Patients with a negative CRM and positive lymph nodes will be recommended to undergo adjuvant chemotherapy as per institutional protocols. It is preferred that these patients do not receive postoperative radiation, as the main objective of the study is to avoid radiotherapy, however, the final decision about postoperative radiation will be left to the discretion of the treating physicians. Patients with a positive CRM irrespective of lymph node status (ie, positive or negative lymph nodes) will be recommended to have postoperative chemoradiotherapy as per the institutional protocols. The follow-up for each study patient will be recorded.

**Figure 2 figure2:**
[figure not shown]
Recommended follow-up for trail participants. MRI: magnetic resonance imaging; pCRM-: negative circumferential resection margin; pCRM+: positive circumferential resection margin; pN-: lymph node negative; pN+: lymph node positive; CRT: chemoradiotherapy; and Chemo: chemotherapy. *No further treatment (bottom, left box): Chemotherapy may be considered at the discretion of the treating oncologist for CRM- and LN- patients for high-risk features such as extramural venous invasion (EMVI).

### Data Collection

Participating surgeons will be required to send the MRI report, operative report, and pathology report to the central study office via facsimile (FAX). All patient documents will be assigned a unique identification number by the study coordinator and will be deidentified by the participating center. The study coordinator at the central office will send regular reminders and updates to all participating physicians and will ensure data collection is complete for each patient. A stand alone FAX machine will be kept in the study coordinator’s locked office and will be used only for the purposes of this study.

## Results

The primary outcome for the study is the positive CRM rate. A positive margin will be defined as any macroscopic or microscopic tumor, discontinuous tumor nodule, or a positive lymph node located within 1 mm of the CRM on final pathologic assessment. We have 30 high volume surgeons at 16 centers participating in this study who see a minimum of 10 new rectal cancer patients over the 18 month time period. Therefore, a minimum of 300 potentially eligible patients will be assessed, and based on the United Kingdom and German studies, it is estimated that 30% (n=90) will be eligible to participate in the study. Assuming an 80% participation rate, it is expected that 75 patients will be recruited over the two year study period.

If seventy-five patients participate, this will provide a 95% confidence interval half-width precision of 6.7% around a point estimate of 10% for the positive CRM rate. If the point estimate for the positive CRM rate is smaller than 10%, the precision around the point estimate will increase.

A Data Safety Monitoring Committee has been organized and will consist of the study statistician, one surgeon, one radiation oncologist, and one pathologist (who are not participating in the study). The study will be stopped if a positive CRM of >10% is reported at any interim assessment, which will occur after every 25 patients accrued in the study.

The secondary outcomes for the study include 2 year LR and disease free survival rates. Descriptive statistics will be used to report: (1) tumor characteristics, (2) positive CRM rate, (3) MRI findings (T-category, N-category, predicted CRM, EMVI), and (4) final pathology (quality of the TME, CRM, T-category, N-category, EMVI). Regression analysis will be performed to assess if any clinical variables are predictive of positive CRM. In addition, comparing the MRI and pathology findings and assessing interobserver agreement for each of the MRI criteria used to identify “good prognosis” tumors will evaluate the accuracy of the MRI interpretation.

This trial is currently recruiting patients.

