**Results:**

We expect to have a minimum of 300 potentially eligible patients, and based on a 30% eligibility rate and 80% participation rate, it is expected that 75 patients will be recruited over the two year study period. A Data Safety Monitoring Committee has been organized, and the study will be stopped if a positive CRM of >10% is reported at any interim assessment, which will occur after every 25 patients accrued in the study.

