### Patient Sample and Recruitment, 3-21 Months

Newly diagnosed rectal cancer patients attending surgical clinics at participating centers will be invited to participate in the study.

The *inclusion criteria* for the study are: (1) diagnosis of rectal cancer (0-15 cm) from the anal verge on endoscopy and proximal extent of tumor at or below the sacral promontory on computed tomography (CT) or MRI; (2) meets all MRI criteria for “good prognosis” rectal tumor as defined by study protocol (see Table 2); (3) 18 years or older; and (4) able to provide written consent.

The *exclusion criteria* for the study are: (1) planned abdomino-perineal resection (APR) based on pretreatment assessment; (2) planned local excision based on pretreatment assessment; (3) T1/early (primary) T2 tumor on preoperative imaging (MRI and/or transrectal ultrasound); (4) suspicious extramesorectal lymph nodes on MRI; (5) unable to undergo MRI due to contraindications (ie, claustrophobia, metal fragments, implanted metal devices); (6) metastatic disease (including extramesorectal lymph nodes, carcinomatosis, liver, lung); (7) pregnancy; (8) inflammatory bowel disease; (9) previous pelvic radiation; and (10) more than one primary tumor.

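### The stated recruitment rates give 72 expected patients, not 75, and the 6.7% half-width is a small rounding slip for 6.8%

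*Protocol article*

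**What the plan says.** The sample-size reasoning is in the Results section of the article and runs in four steps.

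- Source of patients: "We have 30 high volume surgeons at 16 centers participating in this study". Each surgeon is credited with 10 or more new cases in 18 months. From this, "a minimum of 300 potentially eligible patients will be assessed".
- Eligibility: "it is estimated that 30% (n=90) will be eligible to participate in the study".
- Participation and yield: "Assuming an 80% participation rate, it is expected that 75 patients will be recruited over the two year study period".
- Precision: with 75 participants, "this will provide a 95% confidence interval half-width precision of 6.7% around a point estimate of 10% for the positive CRM rate".

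The Results paragraph of the Abstract gives the same chain in short form: "based on a 30% eligibility rate and 80% participation rate, it is expected that 75 patients will be recruited". The Methods heading "Patient Sample and Recruitment, 3-21 Months" sets the recruitment window at 18 months, the same length as the period over which the surgeons' caseload is counted.

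**The concern.** Both places present 75 as the result of the rates quoted beside it, and every input is printed, so the reader can multiply them. The product is not 75. The half-width is likewise a figure that anyone can recompute, and it does not come out at 6.7% to one decimal.

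The article offers no hypothesis test or power calculation. The expected number of patients and the half-width are therefore the whole justification of the sample size. Interim assessments are set after every 25 patients, so 75 is also where a third assessment would fall. Figures that carry this much should agree with their own inputs.

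**Working it through.** **Recruitment.** Inputs, all from the Results section: 30 surgeons, at least 10 new patients each over 18 months, 30% eligible, 80% participating.

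- Assessed: 30 × 10 = 300, as stated.
- Eligible: 300 × 0.30 = 90, as stated.
- Recruited: 90 × 0.80 = **72**. The article states 75, which is 3 more.

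Changing one input at a time, 75 would require:

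- participation of 75 / 90 = 83.3%; or
- eligibility of 75 / (300 × 0.80) = 31.25%; or
- 75 / (0.30 × 0.80) = 312.5, so about 313 patients assessed, or 10.4 per surgeon.

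The mention of a two-year study period beside an 18-month caseload does not explain the gap. Recruitment runs from month 3 to month 21, which is 18 months. Scaling 72 up to 24 months would give 72 × 24 / 18 = 96, not 75.

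**Half-width.** Inputs from the Results section: 95% confidence, rate p = 0.10, n = 75. The article names no formula. The usual planning formula is the normal approximation, 1.96 × √(p(1 − p)/n).

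- n = 75: 1.96 × √(0.09/75) = 0.0679, or **6.8%** to one decimal (6.7% only if truncated).
- n = 72: 1.96 × √(0.09/72) = 0.0693, or **6.9%**.
- n that gives 6.7%: 1.96² × 0.09 / 0.067² = 77.0.

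Other interval methods at n = 75 and 10% do not recover 6.7%. Half the interval width is 6.79% for Jeffreys, 6.90% for Wilson, 6.90% with a t quantile, 7.16% for Agresti-Coull, 7.42% for Clopper-Pearson and 7.46% with a continuity correction. Whole event counts do not recover it under the normal approximation either: 7/75 gives 6.58% and 8/75 gives 6.99%.

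**Size.** The recruitment gap is 3/75 = 4%. The half-width moves from 6.79% to 6.93%, or 0.14 percentage points. The slip in the printed figure at n = 75 is 0.09 points.

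**The case against.** The strongest reply is that nothing of substance is wrong. Both the 300 assessed and the 10 patients per surgeon are stated as minimums, so 72 is the yield at the floor, and fewer than half an extra patient per surgeon would bring it to 75. The precision sentence is conditional on 75 patients taking part, so the recruitment slip does not falsify it. At n = 75 the formula misses the printed figure by only 0.09 points. All of this stands, and it limits the point to a minor one. It does not remove it: both the Abstract and the Results section tie 75 to the quoted rates, and those rates give 72.

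A reader might go further in four ways that the documents do not support.

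- *The trial cannot reach 75, or loses its precision.* The inputs are minimums, and the precision lost at 72 is slight. The assessments at 25 and 50 would still take place, and a third at 75 would fall at about the end of recruitment in any case.
- *The 6.7% figure is unrelated to 75.* It equals the 6.79% result truncated, so a rounding or truncation slip is the likely explanation.
- *The 30% eligibility is optimistic because the two earlier studies had wider entry.* The article gives no eligible fractions for those studies, and the comparison does not run one way. Table 1 limits the German study to tumors at 6 to 12 cm, while this trial takes 0 to 15 cm. The Discussion also says that the German study excluded T1 tumors, although Table 1 lists T1 for it.
- *The symmetric interval is the wrong analysis method.* The article states a planning half-width and names no analysis interval. That choice can properly sit in the full protocol or the statistical analysis plan, neither of which is shown.

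**Conclusion.** The expected recruitment is wrong as written in both places: the stated inputs give 72, not 75. The half-width is a small rounding slip, and should read 6.8% at 75 patients or 6.9% at 72. The recruitment result is simple multiplication of printed inputs and needs no assumption. The half-width result assumes the normal approximation; the alternatives tried at a 10% rate and n = 75 also fail to round to 6.7%. The point is minor. It changes no design decision, stopping rule or conclusion, and 75 patients may still be recruited.

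**What to change.** In both the Abstract and the Results section, either state 72 as the expected recruitment at the minimum of 300 assessed, or keep 75 and restate the input that yields it (about 83% participation, 31.25% eligibility, or about 313 patients assessed). In the precision sentence, give the half-width at a 10% rate as 6.8% for 75 patients or 6.9% for 72, to match the number chosen. The cost is a text correction in two places. The stated precision becomes very slightly less favorable, and nothing in the conduct of the trial changes.

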### Study Overview

This is a 2 year Phase II study to evaluate the safety of MRI criteria to identify “good prognosis” Stage II and Stage III rectal cancer eligible for primary surgery. The safety of the MRI criteria will be evaluated by assessing the positive CRM rate in this “good prognosis” subset of the Stage II and Stage III rectal cancer patients. The MRI criteria will be considered safe if a positive CRM rate of less than 10% is achieved.

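### The >10% stopping rule acts only at every 25th patient, although a 3rd positive CRM within the first 25, or a 6th within the first 50, already settles it

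*Protocol article*

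**What the plan says.** The Results section of the protocol article gives the rule and its timing in one sentence: "The study will be stopped if a positive CRM of >10% is reported at any interim assessment, which will occur after every 25 patients accrued". The abstract repeats both. The threshold matches the safety criterion in Study Overview: "The MRI criteria will be considered safe if a positive CRM rate of less than 10% is achieved".

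The planned size is 75 ("it is expected that 75 patients will be recruited over the two year study period"), so the looks fall at 25, 50 and 75. The Methods headings place recruitment in months 3 to 21. Under Clinical Assessment, patients go to primary surgery once they have consented.

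Three other passages bear on what happens between looks:
- Surgical Assessment says that surgeons "will be encouraged to present cases with positive CRM or incomplete TME at MCC for feedback and audit from the site group".
- Data Collection requires surgeons to send each pathology report to the central study office.
- Pathologic Assessment has that office check the reports for completeness.

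The article does not link a positive CRM seen at the central office to any action by the committee before the next look. It also does not say whether the rate is cumulative or per block of 25.

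**The concern.** A rule of the form observed rate above 10% at n = 25 is a rule about a count. Once the deciding count is reached, later results cannot reverse the decision, yet the rule acts only when the 25th or 50th patient has been accrued. Patients can therefore enter primary surgery under criteria that the trial's own rule has already judged unacceptable.

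The delay is longest when the true margin rate is worst, because the deciding positive then comes earliest. The point concerns when the rule acts, not whether 10% is the right threshold.

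**Working it through.** **The plan's own figure.** The article states a "95% confidence interval half-width precision of 6.7% around a point estimate of 10% for the positive CRM rate". The Wald formula gives 1.96 × √(0.10 × 0.90 / 75) = 6.79%, which agrees with the stated figure to within a tenth of a percentage point. No operating characteristics are stated for the stopping rule, so there is nothing further to reproduce.

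**Deciding counts (cumulative reading).** Smallest x with x/n above 10%:
- n = 25: 2/25 = 8.0% continues; 3/25 = 12.0% stops.
- n = 50: 5/50 = 10.0% is not above 10%; 6/50 = 12.0% stops.
- n = 75: 7/75 = 9.3% continues; 8/75 = 10.7% exceeds.

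Three positives exceed 10% for any denominator up to 29 (3/29 = 10.3%). The first-look result therefore does not depend on all 25 results being available. The look at 75 coincides with the full planned sample, so a stop there spares nobody. The point is confined to the first two looks.

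**Entrants after the deciding positive, first look.** Outcomes are taken as independent with true rate p. The 3rd positive falls on patient k with probability P(k) = C(k−1, 2) p³ (1−p)^(k−3), for k = 3 to 25. The chance of a first-look stop is ΣP(k). The mean number of later entrants, given that stop, is Σ(25−k)P(k) / ΣP(k). With a reporting lag of L entrants, (25−k) is replaced by max(0, 25−k−L). The article gives no pathology lag. L = 4 and L = 8 are assumptions, and the look is taken to be held when patient 25 is accrued. At 75/18 = 4.17 patients a month, they correspond to about 1 and 2 months.

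| True rate | P(stop at 25) | Later entrants, no lag | L = 4 | L = 8 |
|---|---|---|---|---|
| 6% | 18.7% | 7.0 | 3.8 | 1.7 |
| 10% | 46.3% | 8.2 | 4.8 | 2.4 |
| 20% | 90.2% | 11.8 | 8.0 | 4.7 |
| 30% | 99.1% | 15.2 | 11.2 | 7.4 |

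The maximum, with no lag, is 25 − 3 = 22. At 10%, 8.2 / 4.17 is about 2 months of accrual.

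**Not conditional on a stop (no lag).** Multiplying columns two and three gives 0.187 × 7.0 = 1.3 patients at 6%, 0.463 × 8.2 = 3.8 at 10%, 0.902 × 11.8 = 10.6 at 20% and 0.991 × 15.2 = 15.1 at 30% (15.0 before rounding).

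**Second look.** The same calculation was carried forward patient by patient among trials that pass at 25, with the 6th positive as the deciding event. With no lag, the mean number of later entrants given a stop at 50 is 4.9 at 6%, 5.7 at 10%, 8.4 at 20% and 11.8 at 30%. The probability of stopping there is 8.5% at 10% and 6.9% at 20%, so most of the effect lies at the first look.

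**The case against.** The strongest case against is that this is a preference. Scheduled batch looks with an external committee are a common design. The document is a condensed article, and reporting between looks may be set out in a full protocol or a committee charter. Nothing in the article forbids an earlier meeting. That stands as far as it goes: there is no arithmetic error and no contradiction. But the article does fix both the threshold and the timing, and the timing acts later than the rule's own decision. The point does not depend on an omission.

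The effect is also smaller than the no-lag figures suggest. CRM is known only after surgery and pathology, so some later entrants could not be avoided under any rule. At the rates that the Introduction reports for the two reference cohorts (3.3% and 6.0%), a first-look stop is uncommon and the unconditional saving is about 0.3 and 1.3 patients. Both objections are accepted.

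A reader might infer several stronger things that the document does not support:
- **That any 3rd positive settles the matter.** On the cumulative reading it does so only within the first 25. A trial that passes at 25 and has 3 to 5 positives at 50 continues; the chance of that path is 37.5% at a rate of 6% and 34.1% at 10%.
- **That positive margins go unreported between looks.** Pathology reports already go to the central study office. What is missing from the rule is onward notice to the committee and a trigger. The count is also trial-wide; with 75 patients at 16 centers, no single site would usually see it.
- **That every later entrant forgoes preoperative chemoradiotherapy.** The Discussion says that participating centers were not offering it for T1 or T2 tumors, and Table 2 admits definite T2.
- **That later entrants contribute nothing.** They cannot change the stop, but they add to the CRM estimate, the comparison of MRI with pathology, and the 2-year outcomes.

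**Conclusion.** The point holds as an avoidable delay in a safety rule during the first 50 patients. Given a first-look stop, it amounts to about 7 to 15 patients over true rates of 6% to 30% if results were immediate. Under the assumed lag of 4 to 8 entrants it is about 2–4 patients at 6%, 2–5 at 10%, 5–8 at 20% and 7–11 at 30%.

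These figures rest on a cumulative rate, independent outcomes, even accrual of 75 patients over 18 months and, for the lagged figures, a look held when patient 25 is accrued. If the look instead waits for all 25 results, the lag delays the scheduled look about as much as an event trigger, and the saving stays nearer the no-lag figure. The change is worth making because it is cheap and matters most when the criteria perform badly.

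**What to change.** Keep the >10% threshold and the scheduled looks, and add an event trigger:
- State that the rate is cumulative.
- Have the central study office notify the Data Safety Monitoring Committee of each positive CRM when the pathology report arrives.
- Suspend accrual for committee review once the count that makes a rate above 10% unavoidable at the next look is reached: the 3rd positive within the first 25 patients, or the 6th within the first 50.
- Keep all patients already enrolled in the analysis.

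If the thresholds are later revised, derive the trigger counts from the new ones.

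The cost is a sentence or two in the protocol and one onward notification of a report that the office already holds. The probability of stopping at each look is unchanged, because the same outcomes lead to the same decision. When the trial stops early there are fewer patients, and the observed rate is biased somewhat upward because accrual ends on an event: a 3rd positive at patient 13 gives 3/13 = 23%, whereas the same three positives with none among the next 12 patients would give 3/25 = 12%. The report should state that the estimate follows an event-triggered stop.
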